### 3.3. Systemic Biomarkers Analysis

All the biological sample processing and analyses will be conducted at the Biochemistry and Molecular Biology Research Laboratory located within the trial centre. Upon completion of the analyses foreseen in the project, the samples will be destroyed.

Approximately 20 mL of venous blood will be collected in the morning following an overnight fast. Whole blood will be processed immediately for standard hemochromocytometric parameters. Serum will be separated by centrifuging the samples at 3000 rpm for 15 min and subsequently stored at −80 °C under controlled conditions until laboratory analyses are performed. Serum will be thawed immediately before analyses and will be analyzed in duplicate.

#### 3.3.1. Hematochemical Parameters Associated with Nutritional Status

Whole blood analysis will include hemochromocytometric indices (hemoglobin and total lymphocyte count) using a photo-impedance fluorescence cytometmethod. Moreover, the following analysis will be performed by testing every parameter on an integrated analytical photometer (Diacron International S.r.l., Grosseto, GR, Italy):Glucose was assessed by an oxidase/peroxidase system [38].Total cholesterol measured by means of oxidation from a cholesteroxidase to cholest-4-en-3-one [39].Direct HDL cholesterol assessed by a transformation of the HDL portion into a quinone derivative [40].Triglycerides measured with a peroxidase-coupled method [41].Calcium was analyzed using a method based on the o-cresolphthalein complexone test [42].Magnesium was assessed using a direct colorimetric assay based on the xylidyl Blue-I method [43].The Prognostic Nutritional Index (PNI) is a tool used to assess the immunological and nutritional status of patients, particularly in predicting surgical outcomes, cancer prognosis, and postoperative complications. The PNI is calculated using the following formula: PNI = (10 × serum albumin (g/dL)) + (0.005 × total lymphocyte count per mm^3^). The lower the score, the higher the risk (normal nutritional status, low risk: PNI > 38; moderate risk: scores between 35 and 38 severe malnutrition, high risk: PNI < 35).The Nutritional Risk Index (NRI) is a tool designed to assess a patient’s nutritional status and predict the risk of complications associated with malnutrition. It is calculated using the following formula: NRI = (1.519 × serum albumin [g/L]) + (41.7 × current weight [kg]/usual weight [kg]). The lower the score, the higher the risk (no risk: NRI > 100; severe risk: NRI < 83.5).

#### 3.3.2. Assessment of Biomarker of Systemic Oxidative Status

The systemic oxidative status will be analyzed through the following analyses on an integrated analytical photometer (Diacron International S.r.l., Grosseto, GR, Italy).

Total hydroperoxides colorimetric determination of ROMs (Reactive Oxygen Metabolites) (d-ROMs test; Diacron International S.r.l., Grosseto, GR, Italy). In the d-ROMs test, ROMs (primarily hydroperoxides) contained in the biological sample, close to iron, generate alkoxyl and peroxyl radicals, according to the Fenton’s reaction. The radicals, reacting with a chromogenic mixture, oxidize it and transform it into a photometrically measurable coloured derivative. The measurements are reported in arbitrary units (UCARR), where 1 UCARR corresponds to 0.08 mg/100 mL of hydrogen peroxide [40]. Values between 250 and 300 UCARR fall within the normal reference range; 301–320 UCARR are classified as borderline; 321–340 UCARR indicate low oxidative stress; 341–400 UCARR indicate moderate oxidative stress; 401–500 UCARR reflect high oxidative stress; and values exceeding 500 UCARR correspond to very high oxidative stress (Diacron International S.r.l., Grosseto, GR, Italy). The reproducibility of the test reported as CV% is 1.72.The total biological antioxidant capacity (BAP-Test; Diacron International S.r.l., Grosseto, GR, Italy) quantifies the overall pool of endogenous (e.g., bilirubin, uric acid, proteins) and exogenous (e.g., ascorbate, tocopherols, carotenoids, flavonoids) plasma components capable of exerting antioxidant activity and neutralizing reactive radical species. In the BAP test, the biological antioxidant potential of plasma barrier is based on the ability of all antioxidants active to reduce a coloured solution of ferric ions (Fe^3+^) to ferrous ions (Fe^2+^), resulting in a decolouration of the solution that is photometrically detectable. Reference values in µmol/L that are >2200 are intended as “normal antioxidant status”, 2200–2000 are considered a “border line antioxidant status, 2000–1800 are interpreted as “at slight antioxidant deficiency status”, 1800–1600 as “deficiency of antioxidant status”, <1600 as a “high and very high deficiency of antioxidant status” condition (Diacron International S.r.l., Grosseto, GR, Italy). The reproducibility of this test expressed as CV% is 2.32.Calculation of the OSI index to assess the relative antioxidant capacity, namely, the antioxidant capacity normalized for total circulating hydroperoxides. This index is the antioxidative/oxidative stress ratio assessed by the ratio equation: BAP/d-ROMs. We refer to this ratio as the OSI index, which reflects the system’s potential antioxidant capacity [44]. A threshold value of 7.3 was adopted for the BAP/d-ROMs ratio; values below this cut-off were classified as “oxidised,” whereas values equal to or above 7.3 were considered “reduced” [45].

#### 3.3.3. Assessment of Serotonin

Serum serotonin concentrations will be quantified using a fast-track ELISA immunoassay (Mybiosource, San Diego, CA, USA) and read on an absorbance microplate reader (iMARK™, BIO-RAD Laboratory Inc., Hercules, CA, USA). The assay involves an initial quantitative acylation step, followed by a competitive reaction that enables detection at 450 nm. Reference values for serum serotonin range from 70 to 270 ng/mL.

### 3.4. Assessment of Quality of Life

The SF-36 is a self-administered questionnaire designed to assess both physical and mental health-related quality of life (HRQoL). It consists of 36 items grouped into eight scales: Physical Functioning (PF), Physical Role (PR), Bodily Pain (BP), General Health (GH), Vitality (VT), Social Functioning (SF), Emotional Role (ER), and Mental Health (MH). Each scale is rated from 0 to 100, with higher scores indicating a better subjective perception of one’s health. The SF-36 also produces two summary scores: the Physical Component Summary (PCS) and the Mental Component Summary (MCS), which represent overall physical and psychological well-being [46,47].

### 3.5. Assessment of Emotional–Affective Sphere

In this study, widely used and validated instruments were selected from the literature, which have proven to be sensitive and reliable in detecting the constructs under investigation [48,49]. The choice was guided by the need to balance psychometric accuracy and speed of administration, as the instruments are included among numerous other assessment procedures.

In particular, the Beck Depression Inventory-II (BDI-II) and the Beck Anxiety Inventory (BAI) were chosen for their ability to measure depressive and anxiety symptoms in a specific and distinct manner. The BAI, in particular, was constructed to include mainly physiological and somatic symptoms, minimizing overlap with the affective dimensions typical of depression. In addition, the Short Form Health Survey-36 items (SF-36) provides a complementary perspective, allowing the overall impact of symptoms (physical or psychological) on daily functioning to be assessed. This tool allows the analysis to be extended to the domain of perceived quality of life, including physical, psychological, and social components, in line with an integrated approach to worker health. Below is a specific description of each tool mentioned:

(i) The BAI is a paper-and-pencil self-report or interviewer-administered questionnaire that can be administered in an individual format. It allows the severity of anxiety symptoms in adults to be assessed. The scale consists of 21 items, each of which describes a common symptom of anxiety. Respondents are asked to rate how much each symptom has bothered them in the past week on a 4-point Likert scale ranging from 0 (“not at all”) to 3 (“severely”). The total score provides an index of anxiety severity, with higher scores indicating greater symptom intensity [48,50].

(ii) The BDI-II is a self-administered tool consisting of 21 items designed to assess the severity of depression in adults and adolescents aged 13 and older. It is based on the criteria for the diagnosis of depressive disorders listed in the fourth edition of the Diagnostic and Statistical Manual of Mental Disorders (DSM-IV) of the American Psychiatric Association [51]. The scale consists of 21 items scored on a 4-point Likert format (0 = no symptoms, 3 = severe symptoms). It assesses two main domains: somatic–affective manifestations (12 items, e.g., reduced pleasure, low energy, fatigue) and cognitive features (9 items, e.g., self-esteem, self-criticism, feelings of worthlessness). Finally, the BDI-II yields a total score reflecting the overall severity of depressive symptoms [49,50].

### 3.6. Sample Size and Statistical Analysis

This is an exploratory, two-group study (active workers vs. sedentary workers). We planned a total sample of 40 participants (≈20 per group). A priori calculations were performed with G*Power (v3.1.9.7) to inform feasibility for a two-group multivariate comparison approximating Hotelling’s T^2^ (implemented as a MANOVA with two dependent variables, R/H and Xc/H). Under conventional assumptions (two-sided α = 0.05; target power ≈ 0.80; small-to-moderate multivariate effect), a sample size of 35 is typically adequate; therefore, we set N = 40 to accommodate measurement variability and potential attrition while maintaining balanced groups. Although the sample size calculation is fixed to the primary bioimpedance outcomes, the nutritional, biochemical, and psychological variables will be treated as exploratory secondary outcomes. For these, the study aims to estimate effect sizes and variability and to evaluate feasibility rather than to achieve confirmatory statistical power.

Raw R and Xc will be standardized by height (H) to obtain R/H and Xc/H. For each group, we will compute the mean vector and its 95% confidence ellipse on the RXc plane. The primary comparison between active vs. sedentary workers is the displacement of the mean impedance vector assessed with two-sample Hotelling’s T^2^ (reporting T^2^, *p*-value, Mahalanobis distance, and 95% CI for the mean-vector difference). Visualization will include the RXc-mean graph with group ellipses. Covariate-adjusted MAN(C)OVA models will be used as sensitivity analyses to assess robustness. In addition to age and sex—variables inherently related to BIVA interpretation—analyses will adjust for occupational factors (e.g., type of work tasks, years in role, ergonomic load) and lifestyle habits (e.g., smoking, alcohol consumption, physical activity outside work), which may influence hydration, body composition, metabolic state, or psychological indicators. Contemporary reference/tolerance ellipses for interpretation will follow Campa et al. [52] or the most appropriate sex-/age-specific set for our sample.

Standardized phase angle (SPhA), adjusted to sex- and age-specific references, will be analyzed as a continuous endpoint. The primary comparison (active vs. sedentary) will use a two-sample t-test. A sensitivity ANCOVA adjusting for BMI (and other prespecified covariates, if applicable) will assess robustness. The proportion of participants with SPhA ≤−1.65 (≈5th percentile) will be compared between groups using χ^2^ or Fisher’s exact test (reporting risk ratio and 95% CI). Secondary exploratory outcomes, deriving from nutritional, biochemical, and psychological domains’ assessment, will be analyzed with χ^2^/Fisher for categorical variables and t-test/Mann–Whitney for continuous variables depending on normality (assessed with Shapiro–Wilk). Effect sizes with 95% confidence intervals will be reported. Age will be included as a continuous covariate in sensitivity MAN(C)OVA and ANCOVA models. Exploratory analyses will also examine age-related associations with bioimpedance, psychological, and biomarker measures.

Exploratory associations among nutritional indicators (SPhA), bioimpedance parameters, oxidative-stress markers, serotonin, and psychological measures will be examined using Pearson or Spearman coefficients as appropriate. No directional hypotheses are pre-specified for these exploratory analyses; findings will be interpreted as hypothesis-generating.

No missing data are expected because all measurements will be collected during supervised in-person sessions. Data completeness will be verified at the time of assessment. If unexpected missingness occurs, analyses will follow a complete-case approach and the extent of missing data will be reported.

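### The stated sample size of 35 (raised to 40) does not give about 80% power for a small-to-moderate multivariate effect; it does so only for a Mahalanobis distance of about 1.0 to 1.1

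*Protocol article*

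**What the plan says.** The sample-size statement is in section 3.6 of the protocol article. It fixes these elements:

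- **Test:** a "two-group multivariate comparison approximating Hotelling’s T^2", "implemented as a MANOVA with two dependent variables, R/H and Xc/H".
- **Error rates:** "two-sided α = 0.05; target power ≈ 0.80".
- **Effect and resulting size:** "small-to-moderate multivariate effect), a sample size of 35 is typically adequate".
- **Final size:** "We planned a total sample of 40 participants (≈20 per group"), because "we set N = 40 to accommodate measurement variability and potential attrition while maintaining balanced groups".

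No f², Pillai V or Mahalanobis distance is given for the effect, and no attrition rate. The same paragraph ties the calculation to the primary bioimpedance outcomes. It sets aside confirmatory power only for the nutritional, biochemical and psychological variables.

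**The concern.** Test, number of outcomes, α, power and total N are all stated, so the effect size the design can detect is determined. For a two-outcome comparison of two groups of about 20, one would expect 80% power only for a large separation of the mean vectors. A small-to-moderate effect should need a much larger study.

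No other argument for N = 40 is offered, and it concerns the primary comparison, for which a p-value will be reported. A reader who accepts 80% power for small-to-moderate displacement could take a non-significant T² as evidence that the groups' vectors do not differ. If the true effect lies in that range, the test would miss it about 45% of the time in the best case (f² = 0.15, N = 40) and about 90% in the worst (f² = 0.02, N = 35).

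**Working it through.** **Inputs from section 3.6:** two groups of roughly equal size; p = 2 outcomes; α = 0.05; target power about 0.80; N = 35, then 40.

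**Assumed, because the article gives only a verbal effect:** on the MANOVA f² scale, small = 0.02, moderate = 0.0625 to 0.15, large = 0.35. On the Mahalanobis scale, D = 0.2, 0.5 and 0.8 for small, moderate and large.

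**Formulas.** For two groups the T² test is an exact F test with df (2, N − 3). Its noncentrality is

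λ = (n₁n₂/N)·D² = N·f²,

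so that f² = D²/4 when the groups are equal. Power = P(F′ > F₀.₉₅), with F′ noncentral F(2, N − 3; λ).

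**Step 1. Try to reproduce 35 by solving for the detectable effect.**

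| N | df | F₀.₉₅ | λ for 80% power | f² = λ/N | D = 2√f² |
|---|---|---|---|---|---|
| 35 | 2, 32 | 3.295 | 10.60 | 0.303 | 1.10 |
| 40 | 2, 37 | 3.252 | 10.46 | 0.261 | 1.02 |

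The stated 35 corresponds to f² = 0.30. That is twice the upper moderate benchmark (0.15) and close to the large one (0.35). On the D scale, both values exceed the large benchmark of 0.8.

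**Step 2. Power across the assumed range.** For example, at N = 35 and f² = 0.15, λ = 35 × 0.15 = 5.25, which gives power of 48.5%.

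| f² | D | Power, N = 35 | Power, N = 40 | Total N for 80% |
|---|---|---|---|---|
| 0.02 | 0.28 | 10.1% | 11.0% | 485 |
| 0.0625 | 0.50 | 22.5% | 25.5% | 158 |
| 0.10 | 0.63 | 33.9% | 38.7% | 100 |
| 0.15 | 0.77 | 48.5% | 54.7% | 68 |
| 0.16 | 0.80 | 51.2% | 57.6% | 64 |
| 0.35 | 1.18 | 85.7% | 90.6% | 31 |

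A D of 0.2 would need 967 participants.

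**Step 3. Look for another route to 35.**

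- Relaxing α to 0.10 still requires f² = 0.237 (D = 0.97) at N = 35.
- Reading 35 as a per-group figure comes close: f² = 0.15 needs 68 in total, or 34 per group. This conflicts with the planned total of 40.
- A paired t-test with d = 0.5 gives N = 34. So does the within-subject F test of a repeated-measures design with f = 0.25 and correlation 0.5. Neither is the design described.

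No route consistent with section 3.6 yields 35.

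**The case against.** **No number is given, so none can be refuted.** The benchmarks above are not in the document, and the G*Power inputs may be in the full protocol or analysis plan, which the article says exist. It is true that the mapping from label to number is assumed. But no usual small or moderate value on either scale reaches 80% power at 35 or 40, so the choice of benchmark does not decide the matter.

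**Moderate differences on each variable can combine into a large D.** Take d = 0.5 on both R/H and Xc/H, in opposite directions, with a within-group correlation of 0.6 (assumed). Then D = √(2 × 0.25/(1 − 0.6)) = 1.12 and power at N = 35 is 81%; at correlation 0.7, D = 1.29 and power is 91%. This is the best reading for the plan, but it does not rescue the sentence. The article names a multivariate effect, and a D of 1.12 or 1.29 is a large one. Shifts in the same direction at correlation 0.5 to 0.7 give only 26% to 29% power at N = 35.

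**The study is exploratory, and the calculation was meant to inform feasibility.** This limits the consequences. Section 3.6 already promises the Mahalanobis distance and a 95% interval for the mean-vector difference, and nothing in the article says a null result would be read as absence of displacement. Still, the waiver of confirmatory power covers the secondary variables only, and an exploratory label does not make an incorrect power statement correct.

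**Attrition.** A restated figure must allow for it. The 40 includes a margin for losses and section 3.6 specifies complete-case analysis, so the detectable effect should also be given for 35 analysable participants. This point stands and is taken into the fix.

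**Conclusion.** The statement is wrong as written. With the stated test, α and power, 35 participants detect f² = 0.30 (D = 1.10) and 40 detect f² = 0.26 (D = 1.02). For effects from small to the upper moderate benchmark, power runs from 10% to 48.5% at N = 35 and from 11% to 55% at N = 40. The detectable effects follow from the document's own inputs, given roughly equal groups; only the power figures at particular effects rest on the assumed f² and D benchmarks. The design, endpoint and test are unaffected. What fails is the power claim for the primary comparison.

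**What to change.** Keep N = 40 and replace the power sentence in section 3.6 with wording such as:

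> With 40 analysable participants (20 per group), the two-sample Hotelling's T² test at α = 0.05 has 80% power for a Mahalanobis distance of at least 1.02 (f² about 0.26); with 35 analysable, the distance must be at least 1.10 (f² about 0.30). With 40, power is about 55% for f² = 0.15 and about 11% for f² = 0.02.

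Delete the small-to-moderate description and let the numbers stand without a verbal label, since 1.02 to 1.10 ranks differently on the f² and D scales. Add that a non-significant T² will be treated as inconclusive, and that inference rests on the estimated mean-vector difference with its 95% region, which the plan already intends to report.

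The cost is a few rewritten lines. No participants or analyses are added, but the published power claim becomes less favourable.

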### 1.2. Aim and Hypothesis

This exploratory observational study primarily aims to assess whether differences in nutritional status and body composition—as indexed by bioimpedance-based assessment of body cell mass and hydration—exist between sedentary and physically active workers in the food supply chain.

As secondary exploratory aims, we will: (i) assess quality of life and emotional–affective well-being using validated instruments, in order to identify psychological or social critical issues related to work in the food supply chain; (ii) characterize nutritional status and dietary habits to detect potential deficiencies or excesses; (iii) quantify systemic biomarkers of oxidative stress and circulating serotonin levels; (iv) identify risk classes, i.e., subgroups of workers at potentially higher disease risk due to inadequate dietary patterns and/or exposure to occupational stressors; (v) assess sex-related differences in nutritional status, oxidative stress biomarkers, and psychological outcomes, to inform the potential need for gender-specific preventive or dietary recommendations; and (vi) analyze the standardized phase angle (SPhA) as an integrative marker of cellular health and systemic status, and explore its potential associations with nutritional, biochemical and psychological indicators on an exploratory basis.

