### 2.2. Participant Selection for Cohort Study

The patient sample will be recruited at the recruitment centre from workers directly affiliated with the Trial Centre or indirectly connected to it as part of the food supply chain. Patient screening will be carried out by a multidisciplinary team and will aim to determine the subject’s eligibility according to the following inclusion and exclusion criteria.

Inclusion criteria: (i) workers affiliated with the Trial Centre or indirectly connected to the Trial Centre as part of the food supply chain; (ii) adults aged between 18 and 65 years; (iii) willingness to undergo specific tests: assessments of nutritional status, investigations into quality of life and emotional–affective wellbeing; (iv) signed informed consent.

Exclusion criteria: (i) pregnant women will be excluded to avoid physiological changes related to pregnancy affecting the measurements; (ii) workers following specific diets for medical or religious reasons, which may not be representative of the general food supply chain population, will be excluded; (iii) unsigned informed consent.

In addition to excluding pregnant women and individuals following medically prescribed diets, information on chronic medical conditions and medications known to influence serotonin metabolism, oxidative stress, inflammatory status, or body composition will be systematically collected. Rather than excluding these participants, such variables will be treated as potential confounders and incorporated into the analytical strategy (e.g., sensitivity analyses, adjusted models) to maintain ecological validity while minimizing biomarker bias.

Once eligibility has been assessed, participants will be provided with an informed consent form, which they will be required to read and sign before being formally enrolled in the study. The entire process will be overseen by the principal investigator, who will ensure that participants are properly informed and that their voluntary participation is respected, in accordance with the procedures described below.

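### The primary BIVA test is not adjusted for sex or age, so unequal sex mix between active and sedentary volunteers can create or hide a vector displacement

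*Protocol article*

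**What the plan says.** All of this is in the protocol article.

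- **Primary test (Section 3.6).** The article states: "The primary comparison between active vs. sedentary workers is the displacement of the mean impedance vector assessed with two-sample Hotelling", that is, a T² test on R and Xc divided by height. The T² value, p-value, Mahalanobis distance and confidence interval all come from this contrast. Each group gets one mean vector and one confidence ellipse. No covariate or stratum is named.
- **Adjusted models (Section 3.6).** "Covariate-adjusted MAN(C)OVA models will be used as sensitivity analyses to assess robustness". Age and sex are singled out as "variables inherently related to BIVA interpretation". Beyond these two, "analyses will adjust for occupational factors (e.g., type of work tasks, years in role, ergonomic load) and lifestyle habits". Age is placed a second time: "Age will be included as a continuous covariate in sensitivity MAN(C)OVA and ANCOVA models".
- **Reference ellipses (Section 3.6).** Sex- or age-specific reference sets are to be used for interpretation, not in the test.
- **Recruitment (Sections 2.1 and 2.2).** Participation is voluntary, for workers of either sex aged 18 to 65. No matching, quota or stratification by sex or age is stated. The balance mentioned in Section 3.6 concerns group size, about 20 each.
- **SPhA (Section 3.6).** This endpoint is already expressed against sex- and age-specific references.

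**The concern.** The article accepts that sex and age are tied to the impedance vector, then tests the vector with neither in the model. Dividing by height does not remove a sex difference. If active and sedentary jobs attract different proportions of men, the two mean vectors will differ for that reason alone. If the sex shift runs against a real activity difference, the two can cancel.

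The adjusted model does not settle the matter. It puts sex and age together with work tasks, ergonomic load and physical activity outside work. Work tasks and ergonomic load plausibly describe much the same thing as the active/sedentary grouping, so adjusting for them may remove the contrast of interest. No model with only age and sex is specified, and no rule says which result prevails if the two disagree. The primary aim in Section 1.2, a difference in body cell mass and hydration between the groups, therefore rests on the unadjusted figures.

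**Working it through.** **The plan's own figure.** Section 3.6 gives N = 35, raised to 40, at two-sided α = 0.05 and power of about 0.80. The effect is described only in words, so N = 35 cannot be reproduced. Working backwards, two-sample T² power uses F(2, N − 3) with noncentrality λ = (n₁n₂/N)·D². Power of 80% needs D = 1.10 at N = 35 and D = 1.02 at N = 40. I therefore take D = 1.0 as an effect the design can roughly detect: λ = (20 × 20/40) × 1.0² = 10, F(2, 37), power 0.781. The point below does not depend on the origin of N = 35.

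**Inputs.** From the article: 20 per group, two outcomes, α = 0.05. Assumed, because the article gives neither: a male-female vector distance Δ of 1.0 to 2.5 within-sex SD, and the sex mix. The simulation used 10,000 runs per case, bivariate normal vectors with identity covariance within sex, and the sex shift along one axis. Unadjusted T² was compared with the Wilks test for group given sex. Age was not simulated.

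**Spurious distance.** With proportions of men p₁ and p₂ and no activity effect, the apparent distance is

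D = Δ(p₁ − p₂) / √(1 + Δ²[p₁(1 − p₁) + p₂(1 − p₂)]/2).

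For 14 vs 6 men, p₁ − p₂ = 0.4 and the bracket divided by 2 is 0.21:
- Δ = 1.0: 0.4/√1.21 = 0.36
- Δ = 2.5: 1.0/√2.3125 = 0.66

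**False-positive rate, no activity effect, nominal 5%**

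| Men, active vs sedentary | Δ = 1.0 | 1.5 | 2.0 | 2.5 |
|---|---|---|---|---|
| 10 vs 10 | 3.4% | 2.9% | 2.2% | 2.0% |
| 12 vs 8 | 5.7% | 5.8% | 5.6% | 5.6% |
| 13 vs 7 | 8.8% | 11.0% | 12.9% | 14.3% |
| 14 vs 6 | 13.8% | 20.9% | 28.3% | 35.5% |

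The sex-adjusted test stays between 4.4% and 5.2% throughout.

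**Masking, true D = 1.0 opposite to the sex shift.** With 12 vs 8 men the apparent distance is (1.0 − 0.2Δ)/√(1 + 0.24Δ²):
- Δ = 1.0: 0.8/√1.24 = 0.72
- Δ = 1.5: 0.7/√1.54 = 0.56
- Δ = 2.0: 0.6/√1.96 = 0.43

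Simulated unadjusted power is 47.6%, 27.2% and 12.6%, against about 76% adjusted. With 14 vs 6 men it is 28.2%, 9.2% and 3.3%, against about 70%.

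**Equal sex mix, D = 1.02.** Unadjusted power for Δ = 1, 1.5, 2 depends on the direction of the activity effect:
- along the sex axis: 71%, 61%, 47%
- at 45 degrees: 76%, 71%, 65%
- at right angles: 79%, 78%, 78%

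Adjusted power is about 79% to 80%.

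**Price of adjustment, D = 1.0, N = 40.** With k covariates explaining a share R² of group membership, λ = 10(1 − R²) and the denominator df are 37 − k:
- sex and age unrelated to group (k = 2, R² = 0): λ = 10, power 0.779
- 12 vs 8 men (R² = 0.2² = 0.04): λ = 9.6, power 0.761
- 14 vs 6 men (R² = 0.4² = 0.16): λ = 8.4, power 0.700
- wider set, assumed k = 8 and R² = 0.5: λ = 5, power 0.461

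**The case against.** The strongest reply is that the confounders are recognised and adjustment is planned in advance, so the dispute is only about which analysis is called primary. The study calls itself exploratory, Section 4 disclaims causal claims, and SPhA is already sex- and age-referenced. This stands as far as severity goes. It does not remove the point: the headline statistics remain unadjusted, and the only adjusted model described mixes sex and age with covariates close to the exposure.

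A second reply is that large imbalance is not shown. If sex were unrelated to job and half the participants were men, a gap of 8 or more men between groups would have probability 0.017, and a gap of 4 or more 0.27. At 12 vs 8 men the false-positive rate is only about 6%. This also stands, although job-related imbalance is plausible and masking is already marked at 12 vs 8.

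Stronger readings are tempting but unsupported. A reader might infer that the result will be biased; the article gives neither the sex mix nor the male-female distance. A reader might infer that pooling the sexes always costs power; with equal mix the loss is marked mainly when the activity effect lies along the sex axis. A reader might also infer that medication and disease go unadjusted, that secondary outcomes get only unadjusted tests, or that the sex-difference aim (v) has no analysis. Section 2.2 commits to the first ("Rather than excluding these participants, such variables will be treated as potential confounders") through sensitivity analyses and adjusted models. Section 3.6 motivates its adjustment partly by metabolic and psychological measures. The remaining detail may sit in the separate analysis plan named under Data Availability.

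**Conclusion.** The point holds for the primary vector comparison. An unadjusted T² in unmatched volunteers conflicts with the article's own view of sex and age, and unequal sex mix can create or hide a displacement. Under the assumed distances, inflation is negligible at 12 vs 8 men and reaches about 14% to 36% at 14 vs 6. Opposing effects can reduce power from about 76% to between 48% and 13% at 12 vs 8. The sizes rest on the assumed distance, sex mix and direction of effect; the direction of the argument does not. I rate it should-fix: the study is exploratory, adjusted models are planned in some form, and SPhA is largely protected.

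**What to change.** In Section 3.6 and the analysis plan:

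1. Make the primary test the group term of a MANCOVA on (R/H, Xc/H) with sex and continuous age as the only covariates.
2. Report the adjusted mean-vector difference with its confidence interval.
3. Draw the RXc mean graphs and ellipses separately by sex.
4. Keep the unadjusted T² as a supporting analysis and the wider occupational and lifestyle set as sensitivity analysis.

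Age and sex already appear in the planned models, so this is a change of wording with no new measurement. It costs two error degrees of freedom (37 to 35). At D = 1.0, power is 0.779 instead of 0.781 if the covariates are unrelated to group, and about 0.70 instead of 0.78 with 14 vs 6 men. That last loss is the price of separating activity from sex.
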